**Fig. 2 Fig2:**
[figure not shown]
Draft of the template to be used in nursing homes in the HAPPY PATIENT project (patients receiving antibiotics).

Data originating from the registration will be used for quality assessment using quality indicators. In the case of general practice, OOH services and nursing homes, an indicator of antibiotic inappropriateness is considered. Antibiotic prescribing is considered appropriate if it fulfils the following criteria: a) the diagnosis for which this is given might be bacterial; b) it is suspected that the criteria presented by the patient are caused by bacteria; and c) the choice of the antibiotic reflects the local pathogens and resistance patterns in each setting. Anything else is inappropriate. Although antibiotic underprescribing – withholding antibiotic use when the infection is suspected to be of bacterial origin – is also inappropriate, this is negligible in western countries according to the medical literature [18]. Based on the charts used in the registrations the group defined when an antibiotic was appropriate or not. In the case of pharmacies, several indicators have been defined, based on the safety and the appropriate advice given to the patients. Figure 3 describes the example used in OOH services.

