### Statistical analysis plan

Statistical methods for inference in small samples will be used according to a statistical analysis plan. The minimum number of HCPs per APO audit cycle has been estimated based on the assumption that each HCP will register about 25 cases, including either consultations or dispensations, during the audit registration. A decrease of 15% in antibiotic prescribing can be expected after the intervention (from about 40% before to about 25% after). The within-practice correlation coefficient is 0.1. If the comparison is to be performed at the 5% level of significance (two-sided) with 80% power, then the number of HCPs to be included should be 25 per APO cycle. There will be 20 APO cycles in the project (one for each of the 4 healthcare settings involved in each of the 5 target countries). We assume the participation of 500 HCPs in the project and the registration of 25,000 cases.

We will apply the Fisher exact test to the frequencies of prescriptions before and dispensations before and after the audit for each group of professionals and setting/country to test the null hypothesis of no effect of the audit. We will also estimate the effect of the interventions with logistic two-level regression models: a) cases of CAIs and b) HCP participants. Antibiotic prescription will be considered as the dependent variable (yes/no) as well as the concepts of inappropriate prescribing and inappropriate dispensing. These models control for symptoms and duration, as well as for the demand for antibiotics by the patient. Goodness of fit will be assessed using the Wald test of the model, with the deviance test to compare alternative models. Statistical significance will be considered with *P* < 0.05. The data will be analysed using Stata v16.

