The final findings of this quality improvement project will be submitted to a peer-reviewed journal and will be presented in international scientific conferences. The results will be used to inform public health interventions on appropriate antibiotic prescribing and dispensing. Data from all centres will be analysed together and published as soon as possible. The HCPs participating in the study will receive a summary of the main project findings and the perspectives. All data collected as part of this quality improvement project will be shared for common analyses and presentation to the scientific community through publications and conferences.

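### Three tests of one before-after question in the prescribing settings, all at P<0.05 with none deciding, and a sizing outcome that differs from the hypothesised one

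*Protocol article*

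**What the plan says.** All references are to the protocol article.

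- **Statistical analysis plan, tests.** A Fisher exact test compares prescription or dispensation frequencies before and after, for each professional group and setting/country, as a test of no effect. Then: "We will also estimate the effect of the interventions with logistic two-level regression models". These models have cases within HCPs and adjust for symptoms, duration and patient demand. Their outcomes are given as: "Antibiotic prescription will be considered as the dependent variable (yes/no) as well as the concepts of inappropriate prescribing and inappropriate dispensing".
- **Same section, threshold.** One rule covers everything: "Statistical significance will be considered with" P<0.05. No test or outcome is called primary.
- **Same section, sample size.** It rests on antibiotic prescribing falling "from about 40% before to about 25% after", as a single two-sided comparison: "If the comparison is to be performed at the 5% level of significance (two-sided) with 80% power".
- **Abstract (Discussion paragraph) and main Discussion.** The effect hypothesised and expected is a fall in inappropriate prescribing and dispensing. Aims of the study speaks of prescribing or dispensing without that qualifier.
- **Phase 2: audit registrations.** Pharmacy charts record systemic antibiotic dispensations. For their assessment: "In the case of pharmacies, several indicators have been defined, based on the safety and the appropriate advice given to the patients".
- **Ethics and dissemination.** "Data from all centres will be analysed together and published as soon as possible". The sample size and the Fisher tests, by contrast, are per cycle or group.

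**The concern.** With one threshold and no deciding test, a significant result on any of the three can be reported as an effect of the intervention, and the choice can be made after the data are seen. The tests need not agree. A crude and an adjusted analysis can fall on opposite sides of 0.05. Total prescribing can drop while its inappropriate share does not, or the reverse.

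The document also points to two different outcomes as the one that matters: total prescribing in the sample size, inappropriate use in the hypothesis. In pharmacies the sizing outcome cannot be observed as a yes/no before-after contrast, because every recorded case is already a dispensation. At stake is whether the stated 5% level holds even within a single cycle, and which outcome a claim of success would refer to.

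**Working it through.** **1. The plan's own figure.** Inputs from the Statistical analysis plan section: 40% versus 25%, two-sided 5%, 80% power, within-practice correlation 0.1, 25 cases per HCP.

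- Cases per audit, ignoring clustering: n = [1.96·√(2·0.325·0.675) + 0.842·√(0.40·0.60 + 0.25·0.75)]² / 0.15² = 152 (165 with continuity correction).
- Design effect: 1 + (25 − 1)·0.1 = 3.4.
- HCPs: 152·3.4/25 = 20.7, so 21; with continuity correction 165·3.4/25 = 22.4, so 23.

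The stated 25 HCPs (625 cases per audit) is somewhat more than needed and gives about 87% power. Continuity correction plus an unstated 10% loss would give 22.44/0.9 = 24.9, so 25. This gap is not an error. What matters here is that the calculation covers one comparison, on total prescribing.

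**2. Counting the tests in a prescribing cycle.** Fisher on prescriptions; model on prescriptions; model on inappropriate prescribing. The text ties Fisher only to prescription and dispensation frequencies, so the count is three.

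**3. Chance of at least one P<0.05 when nothing has changed, each test valid at 5%.**

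- Independent tests, 1 − 0.95^k: 9.75% for k = 2 and 14.3% for k = 3. These are upper reference points, because the tests are positively correlated.
- Two outcomes, one method. If inappropriate prescriptions are a share s of all prescriptions at rate p, the correlation is √[s(1 − p)/(1 − ps)]. With p = 0.40, s = 0.2, 0.5 and 0.9 give correlations 0.36, 0.61 and 0.92, and error rates 9.4%, 8.7% and 6.8%. With p = 0.25 and s = 0.9 it is 6.7%.
- The three stated tests, from 1,000,000 draws of correlated normal statistics. The correlation between Fisher on prescriptions and the model on inappropriate prescribing is taken as the product of the other two:

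| Correlation between outcomes | Methods 0.7 | Methods 0.9 | Methods 0.99 |
|---|---|---|---|
| 0 | 12.9% | 11.7% | 10.4% |
| 0.5 | 12.1% | 10.9% | 9.6% |
| 0.8 | 10.8% | 9.5% | 8.3% |

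The range is 8.3% to 12.9%. All correlations are assumptions.

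**4. The 5% validity assumption.** A null simulation used 25 HCPs, 25 cases per audit, a 40% rate and correlation 0.1. The size of Fisher on prescriptions depends on how stable each HCP's prescribing tendency is between audits:

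- fully stable: about 3-4%
- correlation 0.8: about 9-10%
- no stability: about 28%

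With an HCP-paired test standing in for the two-level model, at least one of the three tests was significant in about 8-10%, 11-14% and 28-29% respectively. An HCP-stratified stand-in was itself at about 11-13% at correlation 0.8, so validity at 5% is not automatic for a model either. Neither stand-in is the fitted two-level model.

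**5. Sizing outcome against hypothesis.** The sample size uses total prescribing; the hypothesis and expectation use inappropriate prescribing and dispensing. For pharmacies (5 of the 20 cycles) only indicators remain. No error rate is given for them because their number is not stated.

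**The case against.** The strongest reply is that this is a condensed article which refers to a separate statistical analysis plan, and a testing order or alpha rule may stand there. That is fair, and the absence of such a rule here does not show that none exists. It does not remove the conflict between the sizing outcome and the hypothesised outcome, since both are stated in the article.

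The roles are also partly separated: Fisher tests, the models estimate, and the sample size leans towards total prescribing. But one P<0.05 rule covers all of them, and reading total prescribing as primary goes against the Abstract and the Discussion. It remains true that the article states no rule by which any single significant result proves an effect, so the 8-13% is conditional on that reading.

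Three stronger readings are tempting and not supported:

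- **Two outcomes by two methods in every setting.** Fisher is not stated for the inappropriate outcomes, and pharmacies have indicators instead of total versus inappropriate prescribing.
- **A definite error rate for the plan.** The document gives no correlation between outcomes or methods. The size of the Fisher test itself varies widely once clustering is allowed for. Two closely overlapping outcomes alone can give as little as 6.7%.
- **A fixed order starting with total prescribing secures 5% per setting.** It would place the hypothesised outcome behind another one. Each setting also has five country cycles: one test in each gives up to 1 − 0.95⁵ = 22.6% per setting if they are independent. Repetition over cycles is a separate matter from the point made here.

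**Conclusion.** The point holds in limited form. In the prescribing settings the article applies three tests to one before-after question at P<0.05 without saying which decides. It sizes the study on a different outcome from the one it hypothesises, and it leaves pharmacies with more than one indicator and no deciding one. If any significant result counts, the false-positive rate per cycle is roughly 8-13%, against 5% for one named test. This rests on assumed correlations (outcomes 0-0.8, methods 0.7-0.99) and on each test being valid at 5%. The study is not invalidated, but the plan should be settled before the second audit is analysed.

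**What to change.** Before the second audit is analysed, add to the Statistical analysis plan section:

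1. The before-after term of the two-level logistic model is the deciding analysis. The Fisher test, which ignores the HCP clustering that the sample size assumes (0.1), is descriptive. Say how the model allows for HCPs whose prescribing tendency shifts between audits.
2. One deciding outcome per setting, which matches the stated hypothesis and can be observed on that setting's chart. Reconcile it with the sizing outcome. For pharmacies, name one indicator. For nursing homes, check the chart first: the draft template's caption refers to patients given antibiotics, and if only treated patients are recorded, prescription yes/no cannot serve there.
3. The other outcome is tested second in a fixed order, or labelled secondary.
4. Whether the per-cycle or the joint analysis decides, with 5% error claimed only at that level.

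This takes a few sentences and no new data or participants. The downside is that some secondary results can no longer be called significant.

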Due to the limited time allocated for the registration process, only the typical signs and symptoms for RTIs and UTIs will be collected. This may lead to some limitations. Non-biomedical factors that may represent powerful predictors of antibiotic prescription are not considered in this study. This limits the definition used for antibiotic appropriateness in our study as this is based on the different items collected in the registration charts. Another limitation is the lack of studies using the APO method in the pharmacy setting. In addition, the use of over-the-counter antibiotics, still available in some European countries, is not covered in this study.

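### Adjusting the inappropriate-prescribing model for symptoms that help define the outcome dilutes the effect wherever only treated patients are analysed

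*Protocol article*

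**What the plan says.** The Statistical analysis plan section of the protocol article names several outcomes for the same two-level logistic models: "Antibiotic prescription will be considered as the dependent variable (yes/no) as well as the concepts of inappropriate prescribing and inappropriate dispensing". It then sets the covariates: "These models control for symptoms and duration, as well as for the demand for antibiotics by the patient". No outcome or setting is exempted.

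The outcome is defined under Phase 2: audit registrations. "In the case of general practice, OOH services and nursing homes, an indicator of antibiotic inappropriateness is considered". Prescribing counts as appropriate only if three conditions hold: the diagnosis might be bacterial; "it is suspected that the criteria presented by the patient are caused by bacteria"; and "the choice of the antibiotic reflects the local pathogens and resistance patterns in each setting". Everything else is inappropriate. Limitations of the study says of the definition that "this is based on the different items collected in the registration charts", and that the charts hold the typical signs and symptoms of respiratory and urinary infections.

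On who is registered, the text points two ways. Phase 2 asks participants to record every consultation for the selected infections and limits only pharmacies to dispensed antibiotics. The Fig. 2 caption reads "Draft of the template to be used in nursing homes in the HAPPY PATIENT project (patients receiving antibiotics").

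**The concern.** Symptoms sit on both sides of the model: they help decide whether a prescription is classed as inappropriate, and they are held constant when the before-after difference is estimated.

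Among treated patients this matters. A treated patient who fails the bacterial criteria is inappropriate by definition. One who meets them can be inappropriate only through the choice of agent. An intervention that stops antibiotics for patients who fail the criteria therefore changes which symptom pictures appear among the treated, and a model that conditions on symptoms takes part of that change out of the period estimate. The bias is towards no effect, on the component the project chiefly targets: the Background calls reducing unnecessary prescriptions the most effective measure. Nursing homes account for 5 of the 20 audit cycles.

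**Working it through.** **Inputs from the protocol.** Prescribing is expected to fall from about 40% to about 25%. Covariates are symptoms, duration and patient demand. The outcome has three parts (diagnosis, presentation, agent).

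**Inputs assumed (not in the documents).** 25% of patients meet the bacterial criterion and 85% of them are treated in both audits. Treatment of the remaining 75% falls from 25% to 5%. Wrong agent among those meeting the criterion is w = 20% in both audits. Clustering by professional is ignored; it affects precision more than the direction of the bias.

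**1. Calibration to the plan's rates.**
- Before: 0.25 × 0.85 + 0.75 × 0.25 = 0.2125 + 0.1875 = 0.40.
- After: 0.2125 + 0.75 × 0.05 = 0.2125 + 0.0375 = 0.25.

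**2. Treated patients only, recorded symptoms fix the class.** With q the share of treated patients failing the criterion, the inappropriate share is q + (1 − q)w.
- Before: (0.1875 + 0.2 × 0.2125)/0.40 = 0.23/0.40 = 57.5%.
- After: (0.0375 + 0.0425)/0.25 = 0.08/0.25 = 32.0%.
- Crude OR = (0.32/0.68)/(0.575/0.425) = 0.471/1.353 = 0.35.
- Within strata: 100% and 100% if the criterion is failed, 20% and 20% if it is met. The adjusted OR is 1.00 (simulation: 1.01, 95% CI 0.98 to 1.04). The first stratum is also perfectly predicted.

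**3. The same, with better agent choice (w from 30% to 15%).** The within-stratum OR is (0.15/0.85)/(0.30/0.70) = 0.176/0.429 = 0.41. Simulation gives 0.42 adjusted against 0.23 crude. The agent-choice part survives adjustment.

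**4. Treated only, class set by diagnosis, four symptoms imperfectly linked to it** (rates as in step 2, large-sample simulation):

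| Symptom prevalence, bacterial / not | Crude OR | Symptom-adjusted OR |
|---|---|---|
| 60% / 40% | 0.35 | 0.37 |
| 70% / 30% | 0.35 | 0.44 |
| 80% / 20% | 0.35 | 0.58 |
| 90% / 10% | 0.35 | 0.76 |

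**5. Treated only, class set by a count of two or more of four symptoms, the symptoms entered as four separate covariates.** With a 55% cut in treatment of those failing the count and 10% wrong agent, the inappropriate share falls from 56% to 39%. The crude OR is 0.50 and the adjusted OR 0.81. With 625 treated cases per audit, the adjusted effect is significant in about 16% of runs. Under other inputs, a crude OR of about 0.41 becomes 0.70 to 0.76.

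**6. All consultations registered, untreated counted as not inappropriate** (rates as in step 2). The inappropriate share falls from 0.23 to 0.08, so the crude OR is (0.08/0.92)/(0.23/0.77) = 0.087/0.299 = 0.29. The symptom-adjusted OR from simulation is also 0.29.

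**The case against.** A reader might infer that the adjustment removes the intervention effect and that an effective programme in nursing homes would be reported as ineffective. The documents do not support that, for these reasons:

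- **Treated-only registration is not established.** It rests on the caption of a draft template whose figure is not shown. It conflicts with the Phase 2 instruction to record all consultations, and a companion chart for untreated residents cannot be excluded. The analysis section also plans prescription yes/no as an outcome without excepting any setting.
- **Diagnosis is not a planned covariate.** It is a separate chart domain and enters the definition, so symptoms need not fix the class. Step 4 then shows attenuation, sometimes slight.
- **Agent choice is untouched by symptom adjustment**, and the intervention includes treatment guidelines (Table 3). An adjusted OR of 1.00 requires agent choice to stay unchanged.
- **The 16% in step 5 is for one country cycle.** The article says data from all centres will be analysed together. Over five nursing-home cycles, ignoring clustering, the standard error is 0.20/√5 = 0.089; with ln 0.81 = −0.21, power is about 65%.
- **The adjustment has a purpose.** In an uncontrolled before-after study it guards against case-mix differences between the two Februaries, so the crude OR is not an unbiased benchmark either.
- **Unadjusted results may appear elsewhere.** Phase 3 promises reports comparing the two audits on the quality indicators.

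All of this stands and limits the claim. It does not dispose of it. The plan states one covariate set and applies it to an outcome partly built from one of those covariates. The Fisher test is planned for prescription and dispensation frequencies, so no unadjusted test of inappropriateness is stated. Details may sit in the unseen analysis plan, but the article's wording already fixes the adjustment.

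**Conclusion.** The point holds as a conditional one. Wherever inappropriate prescribing is analysed among treated patients only, adjusting for symptoms that help define it attenuates the part of the effect that comes from withholding unnecessary antibiotics.

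The size depends on how closely recorded symptoms fix the class, and that cannot be read from the article because the scoring figure is not shown. Under the assumed inputs, a crude OR of 0.35 to 0.50 becomes anywhere from about 0.37 (weak link) to 1.0 (symptoms fix the class and agent choice does not change). Complete loss is the extreme of that range, not the expected result.

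In general practice and out-of-hours services there is no such harm if all consultations are registered and untreated cases count as not inappropriate. The argument does not extend to pharmacies, whose indicators rest on safety and advice.

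**What to change.** 1. Reconcile the nursing-home template caption with the Phase 2 registration rule, and state which residents are registered.
2. Where all cases are registered, score inappropriate prescribing per registered case (1 = antibiotic given and inappropriate; 0 = no antibiotic, or an appropriate one) and keep the symptom adjustment.
3. Where only treated patients are registered, take the main before-after estimate for inappropriate prescribing from a two-level model without the symptoms that define the outcome. Adjust for age, sex and other non-defining items. Diagnosis is not in the planned covariate set and should stay out of this model. Show the symptom-adjusted model as a sensitivity analysis.

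The cost is a change of wording and one extra model specification; no data collection changes. The downside is that the treated-only estimate is less protected against case-mix differences between the two audits. That should be stated with the result.

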### Data management

All audit data will be collected on paper. The registration templates will be stored securely by each HCP taking part, being only accessible by trial staff and authorised personnel. Once the audit is finished, the registration forms will be transferred to the University of Southern Denmark and will be entered into a database. Data from patients will be anonymously collected from the beginning and no identifiable or personal information about patients will be gathered. HCP participants will be identified with a number. Identifiable data of the HCP (e-mails and the identifier number) will be kept confidential in a separate file and will only be accessible to authorised personnel who require the data to fulfil their duties within the scope of the research project, complying with General Data Protection Regulation requirements.

Data collection will be performed once the HCP has signed the informed consent form. We will only retain participant e-mails and the basic information about the HCP participants during the time this study is running. Anonymised data from the survey will be stored for a minimum of 5 years after publication of the results. Anonymised project data will be shared for common analyses and presentation to the scientific community through publications and conferences. The institutions responsible for the treatment of the data are the coordinator and the institution leading the APO methodology.

